### 2.6. Allocation and Randomization

To conduct the randomization process in a clinical trial, Microsoft Excel 2020 was used to generate a list of random numbers assigned to the participants. Each participant was given a unique number from the list. Those assigned an odd number were placed in the experimental group, while those assigned an even number were placed in the control group. This method ensures a random and equitable distribution of participants across both groups, minimizing bias and ensuring the validity of the clinical trial results.

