### 2.4. Outcomes

In the initial assessment, all variables, including sociodemographic factors, will be measured. Subsequently, all outcome variables will be assessed at the end of the 8-week intervention.

Personal and sociodemographic variables are as follows:Age (years)Sex (male or female)Weight (kilograms), height (meters) and body mass index (kg/m^2^)Time since diagnosis (years and months)Stage of the disease.Tumor location (colon or rectum).Type of chemotherapy and number of cycles.Radiotherapy (yes/no).

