
### 2.5. Sample Size

The sample size calculation was performed using statistical software (G*Power 3.1). The calculation was carried out for a two-independent-group t-test. The effect size (d = 1.11) was estimated from the mean difference on the Chemotherapy-Induced Peripheral Neuropathy (CIPN) Trial Outcome Index (TOI) scale, obtained from Zimmer et al., 2017 [24], due to the similarity of interventions, and from the study by Balnd et al., 2019 [24], where the same scale (EORTC QLQ-CIPN 20) was used in the same group of patients but with a different intervention. A significance level of 0.05 and power of 95% were established. The estimated sample size was 38 subjects. Taking into account a 20% dropout rate based on the previous study [24], the required number of subjects was 44, with 22 subjects in each group.

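### The odd/even allocation rule, as described, does not ensure the planned 22:22 split, and neither it nor a fixed 22:22 list balances chemotherapy type

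*Protocol article*

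**What the plan says.** Section 2.6 (Allocation and Randomization) describes a list of random numbers generated in Excel, with one unique number per participant. The rule is: "Those assigned an odd number were placed in the experimental group, while those assigned an even number were placed in the control group". The range of the numbers is not given, and no block, fixed arm total, stratification or minimisation is mentioned. The section then concludes: "This method ensures a random and equitable distribution of participants across both groups".

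Section 2.5 (Sample Size) relies on equal arms: "the required number of subjects was 44, with 22 subjects in each group".

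Section 2.4 (Outcomes) lists "Type of chemotherapy and number of cycles" among the personal and sociodemographic variables collected at the initial assessment. The article gives this variable no role in allocation.

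For comparing two independent groups, Section 2.8 (Statistical Methods) names Student's t-test and the Mann–Whitney test. Its only multivariable model is a logistic regression for unspecified events of interest, which does not suit a 0–100 CIPN20 score.

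**The concern.** Allocation by the parity of independent random numbers amounts to tossing a coin for each patient. That is a legitimate method, but it ensures neither equal arms nor similar arms. The article claims a property that the described steps do not deliver, and a reader may take it as assurance that group size and case mix were controlled by design.

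Two things could be at stake in a trial of 44. One is power, if the split is far from equal. The other is a chance difference between arms in the chemotherapy received. The primary outcome is neuropathy induced by chemotherapy, and Section 2.2 does not restrict the regimen, so chemotherapy type is a plausible determinant of the score. That is an assumption, because the article does not rank regimens. A sizeable difference in regimen mix would make a small trial harder to interpret, and the two-group tests named in Section 2.8 do not use this variable.

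**Working it through.** **Inputs.** From Section 2.5: N = 44 planned as 22:22; d = 1.11; alpha 0.05 with sidedness not stated; power 95%; two-independent-group t-test; 38 subjects before dropout. From Section 2.6: the odd/even rule with no stated restriction. Assumed, because the article gives no figure: 25%, 50% or 75% of patients receive a given regimen.

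**1. The plan's own figure.** Power comes from the noncentral t distribution with n1 + n2 − 2 degrees of freedom and noncentrality d·√(n1·n2/(n1 + n2)). At 19:19 the noncentrality is 1.11 × √9.5 = 3.42. One-sided power is 95.6%, which reproduces the stated 38. Two-sided, 19:19 has 91.4% power and 46 subjects (23 per arm) are needed. The sidedness, and the step from 38 to 44, are separate matters that do not affect this point. Two-sided 0.05 is used below.

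**2. Chance of the planned split.** With independent parity, the number in the experimental arm is Binomial(44, 0.5).

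| Split | Probability |
|---|---|
| exactly 22:22, C(44,22)/2^44 | 12.0% |
| 26:18 or worse, 2 × P(X ≥ 26) | 29.1% |
| 28:16 or worse, 2 × P(X ≥ 28) | 9.6% |
| 30:14 or worse, 2 × P(X ≥ 30) | 2.3% |

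Section 2.6 says the numbers are unique, so sampling without replacement was also checked. For 44 distinct numbers from 1 to 100, P(22:22) = C(50,22)²/C(100,44) = 16.0%. From 1 to 1000 it is 12.2%. If the list is a permutation of 1 to 44, it holds 22 odd numbers and the split is 22:22 with certainty. Uniqueness alone therefore does not secure the split; the range of the list decides it.

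**3. Effect on power (two-sided, d = 1.11, no dropout).**

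| Split | Noncentrality | Power |
|---|---|---|
| 22:22 | 1.11 × √(484/44) = 3.68 | 94.9% |
| 26:18 | 1.11 × √(468/44) = 3.62 | 94.3% |
| 28:16 | 1.11 × √(448/44) = 3.54 | 93.3% |
| 30:14 | 1.11 × √(420/44) = 3.43 | 91.8% |

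Averaged over all binomial splits, power is 94.4%, a loss of 94.9 − 94.4 = 0.5 points. After 20% dropout in each arm, 23:21 becomes about 18:17 (89.0%) and 28:16 becomes about 22:13 (86.9%), a difference of 2.1 points.

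**4. Balance on chemotherapy type.** Let M of the 44 patients receive a given regimen. The table gives the probability that the arms differ by 20 percentage points or more in its share, by exact enumeration (two binomials for simple randomisation, hypergeometric for a fixed 22:22).

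| Share assumed | M | Simple randomisation | Fixed 22:22, no stratification |
|---|---|---|---|
| 25% | 11 | 14% | 16% |
| 50% | 22 | 18% | 13% |
| 75% | 33 | 14% | 16% |

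The two columns are of the same order. The fixed list is not uniformly better because with 22 per arm the difference moves in steps of 2/22 = 9.1 points. The smallest value at or above 20 is 5/22 = 22.7 points when M is odd and 6/22 = 27.3 points when M is even.

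**The case against.** The strongest reply is that the article does not say the list was unrestricted. A shuffled list of 1 to 44 fits both the unique numbers of Section 2.6 and the 22 per group of Section 2.5, and it gives exactly 22:22. The number range is also a detail that an article may leave to the full protocol. This stands as far as it goes: the 12% and 10% figures are conditional on independent numbers, and a reader should not infer that the arms are known to be unequal. It does not rescue the claim that the method ensures an equitable distribution, because the property depends on a fact the article does not give.

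The second reply is that little follows from this. The power loss is minor. The regimen imbalance is not caused by the parity rule either, since a fixed 22:22 list leaves it about as likely. Both statements are correct. Regimen imbalance is the ordinary result of not stratifying a small trial, and only stratification or adjustment addresses it.

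Three stronger readings are tempting and are not supported:

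- *Chemotherapy type is the main driver of the primary outcome.* The article says that chemotherapy causes neuropathy but does not rank regimens or quantify their effect on CIPN20. The size of any resulting distortion cannot be given.
- *The unadjusted t-test is invalid.* Simple randomisation is unbiased, and the error rate of the test already allows for chance imbalance. Adjustment mainly adds precision and makes the result easier to defend.
- *An odd or even number unmasks the trial.* Section 2.7 says that participants and evaluators could not be blinded, so parity tells them nothing new after allocation. It would matter for the independent statistician only if the randomisation number were also the data identifier. Section 3.3 mentions randomly assigned identification numbers but does not link them to the list.

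**Conclusion.** The point holds in a limited form. Section 2.6 attributes to its method a property that the described steps do not have. Whether the size balance is in fact secured turns on the unstated range of the list. The consequence for power is small either way. The consequence for regimen balance rests on the assumed share of 25% to 75% and on chemotherapy type being related to neuropathy; it is the same in kind with or without a fixed 22:22.

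This is a correction of an overstated claim together with an inexpensive improvement in design and analysis. It is not a threat to the validity of the trial. The absence of covariate adjustment from the article is not itself an error, since an analysis plan that is not shown may provide for it.

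**What to change.** 1. **Patients not yet randomised:** use a computer-generated permuted-block list with randomly varying block sizes, stratified by chemotherapy type, with the categories defined in advance. Stratified blocks keep the split close to 22:22 but need not hit it exactly. For example, with two strata and blocks of at most 4, an unfinished block can leave a difference of 2 per stratum, so the worst case is 24:20, with power 94.8%.
2. **Patients already randomised:** state the number range and whether the list was simple or had a fixed total per arm, and remove the claim that the method ensures an equitable distribution. Sections 2.2 and 2.6 use the past tense while Section 2.3 uses the future tense, so the article does not settle how many patients this covers.
3. **In either case:** prespecify the primary CIPN20 comparison as a model with terms for arm and chemotherapy type, in place of the unadjusted t-test. Section 2.4 already collects the variable.
4. State that the randomisation number is not used as the identifier in the data passed to the statistician, if that is so.

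**Cost:** a new list, a paragraph of text and one extra model term, with no extra patients or visits. If the method changes mid-trial, the change and its date must be documented. Blocking also makes some assignments more predictable in a trial whose evaluators are unblinded; varying the block sizes and withholding them from recruiting staff reduces this but does not remove it.

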### 2.7. Blinding

Due to the nature of the study, participants and evaluators could not be blinded to the intervention. Additionally, the statistical analysis was conducted by an independent statistician who was not aware of the intervention group.

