## Abstract

**Simple Summary:**

Colorectal cancer, a major cause of morbidity and mortality, often requires chemotherapy, which can lead to debilitating side effects such as chemotherapy-induced peripheral neuropathy (CIPN). This study aims to evaluate the benefits of a strength exercise program in reducing CIPN in colorectal cancer patients undergoing chemotherapy. Conducted as a double-blind randomized controlled trial with 44 participants, the study divides them into an intervention group (supervised resistance training and home exercises) and a control group (home exercises only). Primary outcomes will be assessed using the EORTC QLQ-CIPN20 questionnaire, while secondary outcomes include quality of life, body mass index, oxygen consumption, anxiety and depression, fatigue, sleep quality, and various blood parameters. The findings will offer valuable insights into how tailored exercise protocols can improve the quality of life, physical capacity, and treatment outcomes for colorectal cancer patients, advocating for the integration of physical exercise into standard cancer care.

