**Abstract:**

**Background:** Colorectal cancer is a leading cause of morbidity and mortality worldwide, with chemotherapy being a crucial treatment despite its significant side effects, such as chemotherapy-induced peripheral neuropathy (CIPN). Physical exercise has shown potential benefits in mitigating these side effects and improving patients’ overall well-being. **Objective:** This study aims to evaluate the efficacy of a strength exercise program in reducing CIPN in patients with colorectal cancer undergoing chemotherapy, along with secondary objectives including impacts on quality of life, body mass index, oxygen consumption, anxiety and depression, fatigue, sleep quality, and various analytical parameters. **Methods:** A double-blind randomized controlled trial was conducted with 44 participants, divided into an intervention group (supervised resistance training twice a week and home exercises) and a control group (home exercises only). The primary outcome measure was CIPN, assessed using the EORTC QLQ-CIPN20 questionnaire. Secondary outcomes included assessments using the EORTC QLQ-C30, the 6-minute walk test, HADS, FACT-F, and MISS, along with various blood parameters. **Results and Conclusions:** The study will provide insights into the effectiveness of physical exercise in managing CIPN and improving various health parameters in colorectal cancer patients. By developing tailored exercise protocols, this research aims to enhance patient quality of life, optimize treatment outcomes, and reduce the incidence of debilitating side effects, thereby supporting the integration of physical exercise into standard oncological care.

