## 2. Materials and Methods

### 2.1. Study Design and Setting

A double-blind randomized controlled trial was conducted at the Faculty of Nursing and Physiotherapy, University of Salamanca (Spain), following the Consolidated Standards of Reporting Trials (CONSORT) Statement [13]. The current treatment protocol is described according to the recommendations of SPIRIT [14]. The protocol for this trial received approval from the Ethics Committee of the University of Salamanca (record number 1209) and was conducted in accordance with the Declaration of Helsinki. The clinical trial was registered in ClinicalTrials.gov (registration number NCT06404359) (Supplementary File S2, Study flow chart).

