#### 2.3.1. Intervention Group

The intervention group will perform a supervised resistance training program two days/week, combined with a physical activity promotion program to be carried out at home three days/week. All the supervised training sessions will be conducted by a physiotherapist in a healthcare center (Supplementary File S1, Comprehensive description of the intervention).

−Supervised training sessions: There will be two weekly sessions, each one lasting 50 min. Each session will have three distinct parts:
−Warm-up: 10 min of global strength and aerobic exercises at 60% of estimated VO_2_max, focusing on the areas to be primarily targeted during that session.−Resistance training: 6 resistance exercises targeting major muscle groups, with a duration of 30 min. Initial resistance will be set at 70% of the estimated 1-RM. When the participant is able to complete three sets of 12 repetitions at the set weight in two consecutive sessions, the weight will be increased by 10%. Sequenced resistance exercise followed in circuit training fashion with 30 s rest period between exercises and 90 s rest period between sets.−Cooldown/stretching: 10 min of a combination of breathing exercises and stretching.
The detailed description of each of the sessions is presented in the Supplementary Materials, which will be repeated in order and cyclically until the 12 weeks of training are completed.−Physical activity promotion: Participants will complete three weekly home training sessions that will not coincide with supervised training days. Each session will last 20 min, and they will complete two sets of five exercises, with one minute of work and one minute of rest.
−Day 1
Sitting and standing up from a chair.Lateral lunge.Supine bicycle.Elbow flexion with weights.Lateral shoulder raises.−Day 2
Lunge.Quadriceps wall isometric.Glute bridge.Frontal shoulder raises.Wall push-ups.−Day 3
Walking on tiptoes.Squats.Knee-to-chest raises.Abdominal crunch.Shoulder press with weights.

Additionally, all participants should walk for 60 min each day of the week.

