#### 2.4.1. Primary Outcomes

The primary outcome measures are chemotherapy-induced peripheral neuropathy (CIPN). Self-reported neuropathy was evaluated using the European Organisation for the Research and Treatment of Cancer Quality of Life (EORTC QLQ) CIPN20 questionnaire, comprising 20 items categorized into three subscales that assess sensory, motor, and autonomic symptoms. Each item was rated on a Likert scale from 1 ‘not at all’ to 4 ‘very much’. Scores were then converted to a 0–100 scale, with higher scores indicating greater symptom severity.

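### The trial is labelled double-blind, but section 2.7 leaves participants and evaluators unblinded, so the self-reported primary outcome lacks the protection that the label claims

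*Protocol article*

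**What the plan says.** Three places carry the double-blind label:

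- Simple Summary: "Conducted as a double-blind randomized controlled trial with 44 participants".
- Abstract: "A double-blind randomized controlled trial was conducted with 44 participants".
- Section 2.1: "A double-blind randomized controlled trial was conducted at the Faculty of Nursing and Physiotherapy".

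Section 2.7 describes the actual arrangement. It states that "participants and evaluators could not be blinded to the intervention", giving the nature of the study as the reason, and adds that the analysis was done by an "independent statistician who was not aware of the intervention group".

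Section 2.4.1 defines the primary outcome: "Self-reported neuropathy was evaluated using the European Organisation for the Research and Treatment of Cancer Quality of Life", with reference to the CIPN20 questionnaire.

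The arms differ in a way participants can see. Under section 2.3.1, "The intervention group will perform a supervised resistance training program two days/week", led by a physiotherapist, in addition to home exercise. Under section 2.3.2 the control group has home exercise only. Both arms walk daily. Section 3.2 names two limitations, comorbidities and disease progression, and does not mention blinding.

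**The concern.** A double-blind label tells the reader that knowledge of the arm could not have coloured how outcomes were reported or assessed. Here the participant is the rater of the primary outcome and knows the arm. The intervention arm also has regular professional contact that the control arm lacks. Expectation and attention can move questionnaire answers in the direction of benefit without any change in neuropathy, and the comparison of arms cannot separate the two.

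Most secondary outcomes share the exposure. QLQ-C30, HADS, FACT-F and MISS are questionnaires, and the 6-minute walk depends on effort and is run by evaluators who are not blinded.

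Someone who reads only the summary, the abstract or the design section, for example when grading evidence for a review, would credit the trial with a safeguard that section 2.7 says it does not have.

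**Working it through.** **1. The statements on blinding, side by side**

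| Place | Participants | Evaluators | Statistician |
|---|---|---|---|
| Simple Summary, Abstract, section 2.1 | covered only by the label double-blind | covered only by the label double-blind | not mentioned |
| Section 2.7 | not blinded | not blinded | unaware of group |

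The article nowhere defines double-blind as referring to other roles. Even on a generous reading, section 2.7 leaves one masked role, so no pair of masked roles exists that could justify the term.

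**2. What the remaining blinding can do.** A masked statistician cannot favour an arm when choosing exclusions, transformations or tests. The answers are already recorded by then, so a reporting bias in the CIPN20 score passes through the analysis unchanged.

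**3. Illustration of size.** The article states no figure for reporting bias, so there is none to reproduce.

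Inputs:
- 22 per arm (section 2.5, total 44), and 19 per arm (section 2.5, 38 before the dropout allowance, divided by 2).
- Significance level 0.05 (sections 2.5 and 2.8). Sidedness is not stated; two-sided is assumed here, so the nominal rate in the direction of benefit is 2.5%.
- Independent-samples t-test (sections 2.5 and 2.8).
- No true effect, and a differential shift in self-report of b SD in favour of the intervention. **This is an assumption**, shown from 0.1 to 0.5.

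Formula: false-benefit rate = P(T > t(0.975, df)), where T is noncentral t with df = 2n − 2 and noncentrality b × √(n/2).

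- n = 22: df = 42, critical value 2.018. For b = 0.3 the noncentrality is 0.3 × √11 = 0.995.
- n = 19: df = 36, critical value 2.028. For b = 0.3 the noncentrality is 0.3 × √9.5 = 0.925.

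| Assumed shift (SD) | 22 per arm | 19 per arm |
|---|---|---|
| 0 | 2.5% | 2.5% |
| 0.1 | 5.1% | 4.8% |
| 0.2 | 9.5% | 8.7% |
| 0.3 | 16.2% | 14.5% |
| 0.4 | 25.4% | 22.4% |
| 0.5 | 36.7% | 32.3% |

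These rates follow from the open-label design with a self-reported endpoint. They would be the same under any label.

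**The case against.** The strongest reply has four parts.

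- *Participants cannot be blinded to supervised exercise, and section 2.7 says so openly.* This stands. The design is not at fault for it. The defect is that the label in three prominent places says otherwise and that section 3.2 is silent.
- *The comparator is active.* Controls exercise at home five days a week and walk daily, which may narrow the difference in expectation. That is fair, and it is a reason to show small shifts as well as large ones. It does not remove the difference in physiotherapist contact.
- *The percentages rest on an assumed shift.* This stands. They illustrate the risk and do not carry the finding.
- *The documents show a conflict, not which side is wrong.* This stands too. The nature of the study explains why participants are unblinded but not necessarily why evaluators are. If evaluators were in fact masked, section 2.7 is the text to correct. Participants would still rate their own primary outcome unblinded.

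A reader might infer more than the article supports in three ways.

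- *That the trial has no protection against bias at all.* It does have some: statistician blinding is stated.
- *That the statistician's blinding is already broken.* Section 2.6 encodes the arm by parity: "Those assigned an odd number were placed in the experimental group, while those assigned an even number were placed in the control group". The article does not say that this number is in the analysis file. Section 3.3 speaks of randomly assigned identification numbers and does not say whether they are the same. This is a matter to confirm, not an established leak.
- *That the registry entry is wrong as well.* Section 2.1 gives only a registration number, so what the entry says about masking is unknown here.

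**Conclusion.** The point holds, on the text alone. The double-blind label contradicts section 2.7, and nothing in the article reconciles them. As described, the trial is open-label for participants and evaluators with a blinded statistician. Its self-reported primary outcome lacks double-blind protection of reporting and assessment, and the limitations section omits this.

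The size cannot be derived from the article. Under an assumed shift of 0.1 to 0.5 SD, no true effect and two-sided 0.05, the false-benefit rate runs from about 5% to 37% at 22 per arm and from about 5% to 32% at 19 per arm, against 2.5%. Correcting the label leaves that rate unchanged, but readers will then know that they must allow for it. The correction is needed because a headline design property is wrong by the article's own account, on the feature that matters most for a patient-reported endpoint.

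**What to change.** 1. Replace double-blind in the Simple Summary, the Abstract and section 2.1 with open-label, analyst-blinded. If evaluators were in fact masked, correct section 2.7 instead and choose a label that names who was masked.
2. Add to section 3.2 that the primary outcome is self-reported by unblinded participants with unequal physiotherapist contact between arms.
3. Interpret the primary result as patient-reported neuropathy in an open-label comparison.
4. Check that the registry record agrees with the corrected description.
5. As a precaution, confirm that the dataset given to the statistician does not carry the odd/even allocation number. If it does, substitute neutral identifiers and masked arm codes.

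Cost: text edits, one registry check and, at most, one recoded column. No change to sample size, staff or procedures. The downside is a less favourable design label.
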